**Objective:**

This study aims to explore the effects of the refined, commercially-available, humanoid SAR Pepper combined with a tablet PC–based dementia training program (Coach Pepper) versus an exclusively tablet PC–based dementia training program on psychosocial and physical outcomes of people with dementia living at home, including caregivers and dementia trainers. We hypothesize that Coach Pepper has a more positive effect on the primary outcome motivation (stable or decreased apathy) of people with dementia.

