**Assessments**												
	Questionnaires	✓	—	✓	—	—	—	✓	—	—	—	✓
	Sensor data	—	—	—	✓	✓	✓	—	✓	✓	✓	—
	Observation	—	—	—	✓	—	✓	—	✓	—	✓	—
	Interviews, focus groups	—	—	—	—	—	—	✓	—	—	—	✓

^a^Time of enrollment, intervention, and assessment tasks.

^b^Not applicable.

Due to robot Pepper's restricted mobility (navigation is not possible), the robot will stand on a previously defined place in the household (eg, living room) where the person with dementia spends most of the day. Pepper will start communication proactively when the user is in proximity (person in proximity recognition and proactive dialogs) or by a date and time previously entered (time-triggered proactive dialogs). Pepper will encourage the people with dementia to use the tablet PC–based dementia training, and will guide them through the training with speech, gestures, music, and dance. The physical exercise videos as well as the correct answers for the cognitive exercises will be displayed on robot Pepper’s Tablet. Furthermore, Pepper will motivate the participants to use further functions of Pepper itself. However, it is also possible for people with dementia or their relatives to start Coach Pepper at any time.

During the test phase, a dementia trainer comes to the household once a week for one hour to perform the dementia training together with the people with dementia. A nurse or nursing assistant will also come as a visitor in the first and last week of the test period to perform a one-hour observation of the people with dementia. Outside of these times, the participants can independently use Coach Pepper. In addition, all households will receive regular calls from the research team to discuss questions or issues. For all participants, measurements are taken before, during, and after the intervention period (see Multimedia Appendix 1).

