#### Control Group (Tablet PC–Based Training)

The control group will exclusively receive the tablet PC–based dementia training, without the robot. Otherwise, it will be the same procedure as in the intervention group. In total, two people with dementia start the intervention for three weeks, and there will be one week’s break with training for, and adaptations of, the tablet PC–based dementia training for the next two people. Then, a three week test period will happen again with the next two people. This will happen until all 20 people have received the control intervention. Just as in the intervention group, a dementia trainer comes to the household once a week for one hour and a professional caregiver comes twice (first and last week of testing) for observation. Outside these times, people with dementia and their relatives can use the tablet PC training as often as they like. Regular control calls will also be made. For participants in the intervention and control group, it is forbidden during the study to use (similar) devices (eg, robots, tablets, and smartphones) including any cognitive or physical training.

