###### Sensor Data

Furthermore, sensor data from the robot platform Pepper and the theratainment app will be continuously collected during the study period. The objective is to extract key features from the sensor data and investigate correlations with the scores from the used questionnaires (AES, Montreal Cognitive Assessment, and TUG) to apply advanced machine learning techniques to research the potential of developing statistics-based estimators to predict motivation, cognitive state, and mobility/physical activity.

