###### Data Management

The sensor data of robot Pepper will be processed directly for the interaction and not be stored. A connection to Pepper from outside (eg, tablet PC–based training program) is only possible via a secure connection and with a user ID or password. During the study, sensor data is immediately forwarded to the appropriate project partners for processing via secure connections. All sensor data are analyzed anonymously and result in anonymized feature data. The videos themselves are deleted immediately after extracting the features. For each completed dementia training exercise, the tablet PC stores data reflecting the performance of each participant with dementia (eg, wrong/correct answers, quizzes, and time). All data will be analyzed anonymized.

The questionnaires and interviews will be handed over by project members of the social nonprofit organization either personally or via a secure server (protected password) to the Medical University. All personal data of participants will be treated confidentially and interviews will be anonymized during transcription. All participants will be assigned a code. The Medical University and Joanneum Research (research partner) have access to the final data set for analysis. To ensure data quality, all data from paper-pencil questionnaires will be entered into the statistical software by one researcher and will be scanned for errors after data entry by the same person. Furthermore, sample checks for data errors by a second researcher are planned, and the statistician will also perform a plausibility check of the data before starting the analysis.

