### Analysis

#### Quantitative Analysis

Statistical analyses of the results will be performed following the intention-to-treat principle. Descriptive statistics of the data will be presented as a mean and standard deviation, or median and quartile, depending on the nature of the distribution. To describe categorical data, absolute and relative frequencies will be used. To answer the primary question as to whether the motivation differs between the two intervention groups, a median regression is planned. Therefore, it can be adjusted for the degree of dementia and depression. For differences between the intervention groups for the secondary outcomes, the ordinal scale data will be analyzed with median regression. For metric data, a covariance analysis is planned, which also adjusts to degrees of dementia and depression. Changes in pre- and postintervention outcomes concerning relatives will be analyzed by a paired *t* test or a two-tailed Wilcoxon signed-rank test, depending on the distribution of the data. For the sensor data, correlations with the scores of questionnaires will be performed. Furthermore, a skeleton-based analysis of human activity will be applied on the video frames of the physical exercises [57]. The estimated increase of kinetic energy of the movements is intended to provide cues for the increase of motivation [58]. In addition, the video data will be analyzed for nonverbal expressive features which provide analytics about the state of mobility. The significance level will be set to alpha=0.05. For the evaluation, SAS 9.4 (SAS Institute Inc, Cary, North Carolina, United States) will be used.

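### Correlations of training-app features with post-intervention apathy name no term for arm; if the arms are pooled, a robot effect on both can pass for tracking of a person's motivation

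*Protocol article*

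**What the plan says.** All references are to the protocol article.

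- **Analysis.** Quantitative Analysis gives this work one general statement: "For the sensor data, correlations with the scores of questionnaires will be performed". It does not give the type of correlation, the participants included, any covariates, or whether baseline, post-intervention or change scores are used. The same paragraph does name models and covariates (degree of dementia and depression) for the comparisons between intervention groups. It sets alpha at 0.05 without naming an exception.
- **Purpose.** The Sensor Data section says that "sensor data from the robot platform Pepper and the theratainment app will be continuously collected during the study period". The features are to be related to the AES, the Montreal Cognitive Assessment (MoCA) and the Timed Up and Go test (TUG), in order to "research the potential of developing statistics-based estimators to predict motivation, cognitive state, and mobility/physical activity".
- **Who has which data.** Data Management says: "For each completed dementia training exercise, the tablet PC stores data reflecting the performance of each participant with dementia". The tablet training is given in both arms. Robot data can arise in one arm only, since "The control group will exclusively receive the tablet PC–based dementia training, without the robot".
- **Expected effects of the robot.** On use of the training, the text on the Coach Pepper group says: "Pepper will encourage the people with dementia to use the tablet PC–based dementia training, and will guide them through the training". On apathy, the abstract's Objective says: "We hypothesize that Coach Pepper has a more positive effect on the primary outcome motivation (stable or decreased apathy) of people with dementia".

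**The concern.** The sensor aim asks a question about persons: does a feature recorded by the app tell a more motivated person from a less motivated one? A correlation over both arms with no term for arm answers a different question. By the trial's own premises the robot should move both the app feature and the post-intervention AES. Arm is then a common cause of the two, and they correlate over the whole sample even if they are unrelated among people who received the same intervention.

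At stake is the reading of the sensor results. A feature that only separates households with a robot from those without could be reported as a marker of motivation, or used in an estimator, yet have no value for judging motivation in either setting.

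**Working it through.** **Inputs from the protocol article (Sample Size, Quantitative Analysis)**

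- 20 people with dementia per arm, 1:1 allocation
- effect size 0.91, from a mean difference of 10 and an SD of 11 (10/11 = 0.909)
- 80% power, two-sided 5% level
- drop-out of 20% to 30%

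**Reproducing the plan's own figure.** The noncentral t distribution with 20 per arm and a two-sided 5% level gives 80.1% power at 0.91 SD. The stated 80% holds, so 0.91 SD is a fair value for the AES effect that the trial is sized to detect.

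**Assumed.** The robot's effect on an app feature, dX in SD units. The protocol gives no figure, so a range is shown.

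**Model.** Feature X and post-intervention AES Y each have SD 1 within arm and zero correlation within arm. The robot raises X by dX and lowers Y by dY. With 1:1 allocation the variance of the arm indicator is 1/4, so

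- Cov(X, Y) = −dX·dY/4
- Var(X) = 1 + dX²/4 and Var(Y) = 1 + dY²/4
- pooled ρ = −(dX·dY/4) / √[(1 + dX²/4)(1 + dY²/4)]

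For dX = dY = 0.91: 0.8281/4 = 0.207, and ρ = −0.207/1.207 = −0.17.

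For dX = 2, dY = 0.91: 1.82/4 = 0.455, and ρ = −0.455/√(2 × 1.207) = −0.29.

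With 40 participants the two-sided 5% test needs |r| of at least 0.312.

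**Simulation.** 20,000 trials per setting, Pearson test. Two independent sets of runs covered 20 per arm with dY = 0.5 and 0.91; ranges show where they differ.

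| Setting | dX = 0.5 | dX = 0.91 | dX = 1.5 | dX = 2 |
|---|---|---|---|---|
| Pooled ρ, dY = 0.91 | −0.10 | −0.17 | −0.25 | −0.29 |
| Pooled test significant, 20 per arm, dY = 0.91 | 9.4–9.6% | 19% | 36% | 48% |
| Same, 15 per arm (25% drop-out) | 8% | 15% | 27% | 37% |
| Same, 14 per arm (30% drop-out) | 8% | 14% | 26% | 35% |
| Pooled test significant, 20 per arm, dY = 0.5 | 6% | 10% | 14–15% | 19% |

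**With a term for arm.** The partial correlation given arm is significant in 4.6% to 5.4% of trials in every setting.

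**Checks on the mechanism.** If dY = 0 or dX = 0, the pooled test stays at about 5%. For a feature recorded only in the robot arm (20 people), the plain correlation is significant in 5.1% of trials, so no correction is needed there.

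**The case against.** The strongest reply is that the article states nothing wrong. It gives the analysis one sentence and says neither that the arms are pooled nor that they are not. A condensed article may leave the correlation model to a fuller plan that is not shown. This stands, and the point is therefore conditional on pooling. It does not remove the point: the paragraph names a method for this aim and covariates for the other analyses, and the method as named does not separate the arms.

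Further objections also stand and limit the scope.

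- **Not a type I error.** A reader might infer that the error rate of the test exceeds 0.05. If the robot moves both variables, the correlation over all participants really is non-zero, and finding it is not a false rejection. The fault is that this correlation is not the quantity the aim asks about.
- **No selection rule.** A reader might infer that features will be chosen by p-value and passed to the estimators. The article says only that correlations will be investigated and the potential for estimators explored.
- **Not all sensor data or scores.** Robot-only features exist in one arm, and baseline scores carry no systematic arm effect under randomisation. The stated hypothesis concerns motivation, so no arm effect on MoCA or TUG is predicted.
- **A special case.** Zero association within arm isolates the mechanism, but nothing in the protocol says to expect it. The larger rates need assumed feature shifts of 1.5 to 2 SD. With 0.5 SD on both variables the rate is about 6%, and with 0.91 SD on both about 81% of trials would show nothing significant.

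**Conclusion.** The point holds in a narrow form: app features recorded in both arms, correlated with post-intervention AES, if the arms are pooled and the robot shifts both. In that case the correlation mixes the effect of arm with person-level tracking. At the protocol's own 0.91 SD on both variables, about 19% of trials would show a significant correlation from arm alone, against about 5% with arm adjustment. The range is about 10% to 48% for feature shifts of 0.5 to 2 SD, which are assumptions.

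This concerns a secondary, exploratory analysis. A reader might infer a threat to the main result, but the primary AES comparison between groups does not use these correlations and is untouched. The change is optional.

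**What to change.** In Quantitative Analysis, replace the general statement on sensor data by something like:

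> For training-app features recorded in both groups, partial correlations with post-intervention or change scores of the AES, MoCA and TUG will be computed with adjustment for intervention group and shown by group. Features recorded only by the robot will be analysed within the Coach Pepper group.

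In the Sensor Data section, add that the accuracy of any estimator will be reported within each arm, so that knowing who had the robot cannot count as predicting motivation.

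Arm is already recorded, so no new data are needed. The cost is one degree of freedom (37 instead of 38 with 40 participants), and some correlations will look weaker than the pooled ones. A feature that does track motivation among people given the same intervention keeps that association after adjustment.

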#### Qualitative Analysis

The qualitative interviews (individual interviews with people with dementia and relatives; focus groups with caregivers and dementia trainers) will be organized in the MAXQDA software program (VERBI GmbH, Berlin, Germany), and coded and analyzed by means of qualitative content analysis according to Schreier 2012 [59] by the Institute of Nursing Science.

## Results

As this is a study protocol with the study still in the intervention stage, no results are available as of yet. The study started in May 2019 and 18 participants with dementia (8 per group) have already finished the intervention. The study will end in spring 2020.

## Discussion

The overall aim of this study is to explore the effect of a SAR on psychosocial and physical outcomes of people with dementia living at home, including caregivers and dementia trainers. We hypothesize that the robot has a positive effect on the primary outcome motivation (stable or decreased apathy) of people with dementia.

### A Lack of Commercially Available and Tested Socially Assistive Robots

Research with SAR is a relatively young field [60], especially in people with dementia. A systematic review by Ienca et al [61] focusing on intelligent assistive technologies (including SAR) for people with dementia identified only 17/539 studies that included SAR. Furthermore, many studies were testing SAR in an (early) prototype stage [23,62]. Bedarf et al [62] identified in a review focusing on older people that, in general, only 6/107 robots were already commercially available. Buhtz et al [23] identified 3/13 SAR which are commercially available for older people in home care. In our study, the commercially available robot Pepper by SoftBank will be tested, which was refined for home care by our research team before this study according to the results of a qualitative study using a content analysis of interviews that included 80 participants (not yet published), and a first prototype test in home care with 12 participants (ClinicalTrials.gov Identifier: NCT03823066, results not yet published), including people with dementia, caregivers, and dementia trainers. The refined robot is illustrated in Figure 1. According to Alzheimer’s Disease International [1], in the absence of a medical solution for dementia, we need more research and innovation around care.

### Reasons of Institutionalization and Socially Assistive Robots as Nonpharmacological Home Care Intervention

Most often, research with robots like SAR is performed in laboratories and institutional settings such as nursing homes [13,15,63]. However, the home care setting is of high importance [1] because about 80% of people with dementia, especially in the early stages of the condition, receive care at home mainly through their relatives, with or without professional support [6,64,65]. Caregiver burden and the inability of informal caregivers to perform care on the person with dementia, beside neuropsychiatric symptoms/BPSD (especially apathy [66]), care dependency (in various ADL), mobility and cognition problems of the person with dementia, are some of the main reasons for institutionalization (eg, nursing home) [66-68]. Andel et al [69] stated that people with dementia are admitted earlier into a nursing home than people without such an illness. This situation shows that it is important to support caregivers of people with dementia in home care so that people with dementia can stay at home as long as possible. Our study includes cognitive and physical training by robot Pepper that belongs to the area of nonpharmacological interventions, where studies show that cognitive interventions may have a positive benefit for cognition and ADL, and physical training may improve or maintain ADL and may have a benefit for neuropsychiatric symptoms/BPSD [70-73].

### Relevance to Include Personal Views of People With Dementia

In our study, we included the personal experience of people with dementia because from the point of view of older care-dependent people, there is a scarcity of knowledge about the use of robots like SAR in real care situations [63]. It is highly recommended to include people with dementia and cognitive impairment in the design iteration cycles [74-77] because their feedback is very relevant for the appropriate and user-friendly development of novel technologies [76]. Furthermore, people with dementia are indeed able to learn to make use of robot technologies [77,78].

### Limitations of the Study

The study focuses only on people with mild to moderate dementia. Therefore, the results cannot be used for people with severe dementia. People with frontotemporal dementia were not included in the study because of known aggressive behavior. Therefore, we will not be able to obtain information as to whether people with this dementia type may benefit from a robot-based intervention. The study is performed only in home care, and results cannot be generalized to other settings, like nursing homes or hospitals.

Results and information of the ongoing study will be disseminated via our project homepage.

## Appendix

Multimedia Appendix 1 Measurements and time of data collection.

## Abbreviations

ADL: activities of daily living
AES: Apathy Evaluation Scale
BPSD: behavioral and psychological symptoms of dementia
NPI: Neuropsychiatric Inventory
SAR: socially assistive robot(s)
TUG: Timed UP and GO Test
